### Assignment of interventions

#### Allocation sequence generation

Within 24 h of birth, once written consent is obtained, eligible babies will be randomised into one of eight treatment conditions (Table 1) at equal allocation ratio via a secure web-based interface. Randomisation will be stratified by gestation (32^+ 0^ to 33^+ 6^; 34^+ 0^ to 35^+ 6^ weeks), recruitment centre (each centre has different nutrition practices) and sex (this influences growth and body composition), using variable block sizes of 8 or 16. Twins and triplets will be randomised as separate babies.

**Table 1 Tab1:** Factorial design randomisation table. + means the baby receives this intervention; − means the baby does not

Condition	Parenteral nutrition (i)	Milk supplement (ii)	Taste/smell (iii)
1	**+**	**+**	**+**
2	**+**	**–**	**+**
3	**+**	**+**	**–**
4	**+**	**–**	**–**
5	**–**	**+**	**+**
6	**–**	**–**	**+**
7	**–**	**+**	**–**
8	**–**	**–**	**–**

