### Statistical considerations

#### Sample size

Unlike multi-arm, parallel RCT or comparative experiments, factorial experiments are designed to estimate main effects and their interactions [18]. Each main effect and interaction analysis is, therefore, based upon the total sample size which is chosen to be large enough to detect all primary outcomes [18]; having more factors does not increase total sample size [18]. A total of 480 babies (*n* = 240 per intervention arm) will provide ≥90% power at an overall type 1 error rate of 5% to detect a minimal clinically significant difference in % fat mass at 4 months’ correct age of 3% (lower 95% confidence interval) for parental nutrition and milk supplement interventions, or to detect a reduction in median time to full enteral feeds from 10 to 7 days (hazard ratio 1.43) with the taste/smell intervention. This sample size has assumed a standard deviation of 4% in % fat mass, with Bonferroni corrections to each of the three tests (i.e. alpha per main intervention effect = 0.0167). Allowing for 10% loss to follow-up, we aim to recruit 528 babies (*n* = 66 per randomised condition). The expected effect size is based on an estimated 3% increase in % fat mass in moderate to late preterm infants compared to term infants [7] and an estimated 27% fat mass in term infants at 4 months of age [19]. There are no good data on % fat mass beyond 4 months of age; therefore, this age has been used as the primary outcome.

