#### Statistical analyses

Statistical analyses will be performed using SAS version 9.4 (SAS Institute Inc., Cary, NC, USA). The main intervention effects will be evaluated on an intention-to-treat basis. All eligible infants will be analysed according to the assigned condition at randomisation, adjusting for stratification factors and the non-independence of multiple births. Other baseline confounders that are closely associated with the outcomes will be considered in the model if there is evidence of group imbalance by chance (≥ 10%). For the primary outcomes, % fat mass at 4 months’ correct age will be analysed using generalised linear regression with the model-adjusted mean difference. Time to full enteral feeds will be analysed using Cox proportional hazards model with the adjusted hazard ratio. The between group difference will be estimated with 95% confidence interval and *p*-value. An overall type I error rate of 5% will be maintained controlling for multiple comparisons. Secondary outcomes will be evaluated using regression models appropriate to their distributions with similar model adjustment.

Primary analyses will focus on the main effect of each intervention against its comparator, controlling for co-intervention in the same condition. Secondary analyses will test for possible interactions between the main effects. Additional, per protocol analyses will be conducted on those babies without protocol deviations. Missing data will not be imputed on the study outcomes, as the key assumption of missing at random is unlikely to hold in the analysis populations. Sensitivity analyses will be conducted, however, using a multiple imputations method to explore the potential impact of missing data on the primary outcome.

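### Covariates beyond the stratification factors enter the primary models only if imbalanced by an undefined 10% or more; name the prognostic ones in advance and adjust for them whatever the balance

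*Protocol article*

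**What the plan says.** Under Statistical analyses, the protocol article commits to analysis by assigned condition, "adjusting for stratification factors and the non-independence of multiple births". The stratification factors, under Allocation sequence generation, are gestation in two bands, "recruitment centre (each centre has different nutrition practices) and sex (this influences growth and body composition". These enter every model.

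A second rule covers everything else: further baseline variables strongly related to the outcomes "will be considered in the model if there is evidence of group imbalance by chance", followed in parentheses by a threshold of 10% or more. A further covariate must therefore pass two tests, association with the outcome and observed imbalance, and passing both leads only to consideration. The candidate covariates, the scale of the 10% and the groups to be compared are not given. The rule applies to the linear model for % fat mass and the Cox model for time to full enteral feeds, and similar adjustment is carried to the secondary outcomes.

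**The concern.** Under randomisation every baseline imbalance is a chance imbalance, as the sentence itself acknowledges. What adjustment gains depends on how strongly the covariate predicts the outcome. The rule asks for a prognostic covariate and then leaves it out when the arms happen to be balanced on it. In a linear model that is when the unadjusted standard error is too large for the data at hand, because it still carries outcome variation that the covariate would explain. In a Cox model, omitting a prognostic covariate moves the hazard ratio toward 1, so which covariates enter also changes the quantity being estimated.

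The rule also makes the primary model depend on a comparison of the arms, on an unstated reading of 10% and on judgement. Residual prognostic information is plausible: the Background attributes delayed feeding partly to immaturity, while gestation is adjusted only in two-week bands.

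**Working it through.** **Inputs.** From Sample size: "A total of 480 babies" (240 per level of each factor); SD of % fat mass 4; planned difference 3 points; hazard ratio 1.43; "alpha per main intervention effect = 0.0167". Two-sided testing is assumed because sidedness is not stated. Covariate strengths and the reading of 10% are assumptions, shown as ranges.

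**The plan's own figure.** It states that the sample "will provide ≥90% power at an overall type 1 error rate of 5"%.
- % fat mass: SE = 4 × √(2/240) = 0.365; 3/0.365 = 8.22; the critical value is 2.394; power exceeds 99.9%.
- Time to full feeds, every baby having the event (Schoenfeld): ln(1.43) × √480 / 2 = 3.918; power = Φ(3.918 − 2.394) = 93.6%.

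Both reproduce the stated 90% or more.

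**How often chance triggers the rule (240 versus 240).**
- 10% as a standardised difference of 0.1: SE = √(2/240) = 0.0913; z = 1.095; P = 0.273. For five independent covariates, at least one is flagged with probability 1 − 0.727⁵ = 0.80.
- 10% as percentage points on a binary covariate: at 50% prevalence SE = √(2 × 0.25/240) = 0.0456, z = 2.19, P = 0.028; at 20% prevalence SE = 0.0365, z = 2.74, P = 0.006.

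The rule is therefore triggered often or almost never, depending on an unstated definition.

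**Type I error, linear model.** Simulation, 50,000 runs per scenario, one continuous covariate, threshold 0.1, nominal 1.67%. R² is the share of variance explained beyond the stratification factors.

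| R² | Always adjusted | Rule, mechanical | Rule, free choice when imbalanced |
|---|---|---|---|
| 0.1 | 1.67% | 1.45% | 1.94% |
| 0.2 | 1.56% | 1.15% | 1.83% |
| 0.3 | 1.69% | 1.03% | 1.93% |

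Across repeat runs the mechanical rule ranged from about 0.8% to 1.45% and free choice from about 1.7% to 1.9%.

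**Power and precision, % fat mass.**
- At 3 points: above 99.9% under every approach.
- At 1.34 points (90% power unadjusted), R² 0.1/0.2/0.3: rule 91/92/94%, always adjusted 93/96/98%.
- At 1.2 points, over the same R² range: rule about 83–87%, always adjusted about 86–94%.
- At 1.0 point: rule 65/67/69%, always adjusted 68/74/81%.
- Half-width of the 95% interval: 1.96 × 0.365 = 0.72 points unadjusted; multiplied by √(1 − R²), it is 0.68/0.64/0.60 with adjustment.

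**Power, time to full enteral feeds.** Simulation, 3,000 runs per scenario, 480 events, hazard ratio 1.43 conditional on the covariate.

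| Covariate log-HR per SD | Unadjusted HR | Unadjusted power | Rule | Always adjusted |
|---|---|---|---|---|
| 0.3 | 1.395 | 88% | 90% | 94% |
| 0.5 | 1.353 | 80% | 86% | 94% |
| 0.7 | 1.307 | 69% | 77% | 93% |

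The SE of the treatment log hazard ratio is 0.092–0.093 with or without adjustment, so the loss comes from attenuation. Check at 0.7: ln(1.307)/0.092 = 2.91; Φ(2.91 − 2.394) = 70%, close to the simulated 69%.

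**The case against.** The strongest defence is that the rule is narrow. Gestation band, centre and sex are always in the model, prognostic association is already required, and a covariate list is ordinary SAP content. All of that stands, and the missing list is not the point. The point is that the protocol states an entry rule, and an SAP that follows the protocol inherits it.

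Several stronger readings are tempting, and the document does not support them.
- *No baseline covariate enters unless imbalanced.* The stratification factors always do.
- *The rule inflates type I error.* Applied mechanically it is conservative. Only free choice pushes it above nominal, and then slightly.
- *The trial loses power on % fat mass as planned.* At 3 points it does not; the losses are at differences the plan does not use.
- *The Cox analysis loses precision.* The standard error hardly changes; the estimate attenuates.
- *Chance flags a covariate 57% of the time.* That figure compares two of the eight conditions at 66 each, whereas the primary analyses are main effects.
- *The model will be picked with outcomes in view, and separately for each factor.* The trigger is baseline balance, which could be checked on coded arms, and the text does not say that balance is judged factor by factor. Nothing in the article rules either out, but neither is stated.

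The Cox figures also take 1.43 as the hazard ratio conditional on the covariate. If the 10-day and 7-day medians are meant as population-wide figures, the unadjusted test keeps about 94% and the rule forgoes extra power instead of falling below 90%.

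**Conclusion.** The concern holds in limited form. For covariates beyond the stratification factors, the protocol fixes a trigger that is wrong in principle, undefined in scale and discretionary in effect. The primary model then depends on chance: about 27% per covariate on one reading of 10%, 3% or less on another.

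Error control is not seriously threatened. The sample size is not wrong on this point, and % fat mass keeps its planned power. The costs are a conservative test and a wider interval for % fat mass, lost power if the true difference is well below 3 points, and, for time to full feeds, power of about 90/86/77% against 93–94%. These sizes rest on one continuous covariate, 10% read as a standardised difference of 0.1, residual R² of 0.1–0.3, covariate log hazard ratios of 0.3–0.7 per SD, an event in every baby and a conditional hazard ratio of 1.43. None of the covariate strengths is in the document, and only a strong residual predictor gives the larger Cox losses. The change is worth making because it is nearly free.

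**What to change.** Delete the imbalance trigger. Before outcomes are compared by arm, name a short list of prognostic baseline covariates and adjust for that list, together with the stratification factors, in all three main-effect models whatever the observed balance. Gestational age in continuous form and birthweight z-score are natural candidates: gestation is needed for eligibility and stratification, and weight is measured at birth. Multiple birth is already handled as clustering and need not be listed. Baseline balance can still be described without driving the model.

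The cost is a change of wording, with no new data and no change to the sample size. The downsides are a few model degrees of freedom and a Cox hazard ratio that must be reported as conditional on the listed covariates.

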#### Recruitment

Parents of eligible babies will be approached by a member of the research team for recruitment antenatally where appropriate; if antenatal recruitment is not possible than families will be approached after birth upon admission to the neonatal unit. Recruitment will need to occur within 24 h after birth for the baby to be randomised. Formal written consent will be required before babies enter the study. Consented babies who are admitted to the neonatal unit and require an intravenous line will be immediately randomised to one of eight conditions (Table 1). If parents decline consent, nutritional care will be according to the plan of the attending physician.

### Data collection methods

#### Body composition

Body composition will be measured at 4 months’ corrected age when infant adiposity is predictive of childhood fat mass [17]. Measurement using air displacement plethysmography (APD) system PEA POD (COSMED., Concord, CA, USA), will occur as close to discharge as is feasible and at 4 months’ corrected age as the preferred method for determining body composition. Subscapular, triceps, biceps, abdominal, thigh and suprailiac skinfold thickness (mm) will also be measured in triplicate by trained personnel at 4 months’ corrected age using standardised skinfold calipers and the mean value recorded.

#### Anthropometry

Weight, length and head circumference will be measured at birth and every week until discharge and at 4 months’ corrected age.

#### Monitoring of nutritional intake

Total enteral and intravenous intakes will be recorded daily until discharge, or up to 28 days of age, or until baby begins receiving breastfeeds with less than full tube feed top-ups, as the quantity of breastmilk received cannot be quantified. Mean daily protein and energy intakes will be calculated based on actual intakes. Full enteral feeds will be defined as 150 mL.Kg^− 1^.d^− 1^ or exclusive breastfeeding. Energy and protein intakes will be calculated using breastmilk composition for the first week of life (57.1 kcal and 1.9 g protein/100 ml) and for weeks 2–8 (65.6 kcal and 1.27 g protein/100 ml) [20]. For all reporting of neonatal nutrition and growth outcomes, we will use the StRoNNG checklist [21]. Time to full sucking feeds will be defined as until removal of the nasogastric tube for at least 24 h or until discharge home, whichever is the sooner. Any baby discharged home on gastric tube feeds will be excluded from this analysis.

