Taste and smell also may be important in food tolerance. Even before ingestion of food, taste and smell initiate metabolic processes through secretion of hormones such as insulin and ghrelin [12]. However, the role that these senses play is not usually considered in the care of preterm infants, despite preterm infants having functional taste receptors from 18 weeks’ gestation and flavour perception from around 24 weeks’ gestation [13]. Taste receptors in the mouth relay signals to the brainstem and higher centres, leading to activation of the cephalic phase response and the release of appetite hormones in saliva [14]. These salivary hormones are postulated to play a role in metabolism [14]; indeed, impaired oral nutrient sensing is associated with increased energy intake and a greater body mass index [15]. A pilot trial exposing very preterm infants to the taste and smell of milk before each tube-feed found that infants in the intervention group reached full enteral feeds and tended to have the nasogastric tube removed at an earlier gestational age [16]. These data suggest that the simple intervention of providing taste and smell stimuli before gastric tube feeds may enhance feed tolerance.

Thus, we hypothesise that:Early nutrition supplementation including protein will prevent a protein deficit leading toBody composition at 4 months’ corrected age similar to that of term-born children, andImproved neurodevelopmental outcomesExposure of MLPT babies to taste and smell before each feed before establishment of full breastfeeds will decrease time to full enteral feeds and full sucking feeds.

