### Interventions and comparators

(i).Parenteral nutrition vs. intravenous dextrose solution;(ii).Supplemental milk (donor breastmilk if available, else infant formula) vs. only mother’s milk;(iii). Exposure to taste and smell of milk before every gastric tube feed vs. no exposure (milk administered only via gastric feeding tube).

All babies will receive nutrition according to individual neonatal unit practices. The first two interventions only apply until the baby is established on full enteral feeds with mother’s milk. Babies randomised to receive taste and smell before tube feeds will continue to receive this intervention until the baby is no longer receiving any gastric tube feeds. The goal for all babies enrolled in the study is to transition to full feeds of mother’s breast-milk as soon as possible.

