#### Secondary outcomes

Time to full sucking feeds; number of days in hospital; body composition at discharge; growth: length, weight and head circumference Z-scores and Z-score change from birth to 4 months’ corrected age and at 2 years’ corrected age; developmental assessment at 2 years’ corrected age; breastfeeding rates; nutritional intake from birth to full enteral feeds or until 28 days of age.

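### Excluding babies discharged home on tube feeds from time to full sucking feeds is an outcome-dependent, post-randomisation exclusion that biases this secondary comparison, mainly towards no effect

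*Protocol article*

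**What the plan says.** Protocol article, Secondary outcomes, opens its list with "Time to full sucking feeds; number of days in hospital". The Background section makes the first of these part of the taste/smell hypothesis: exposure "will decrease time to full enteral feeds and full sucking feeds". That intervention also runs for as long as the outcome is open, because under Interventions and comparators babies "will continue to receive this intervention until the baby is no longer receiving any gastric tube feeds".

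Monitoring of nutritional intake defines the outcome. The clock stops when the nasogastric tube has been out for at least 24 hours, "or until discharge home, whichever is the sooner". The next sentence adds the rule at issue: "Any baby discharged home on gastric tube feeds will be excluded from this analysis".

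Statistical analyses sets the general principle: "The main intervention effects will be evaluated on an intention-to-treat basis", and "All eligible infants will be analysed according to the assigned condition at randomisation". Secondary outcomes are to be modelled with similar adjustment. No exception is made there for babies discharged on a tube. The multiple-imputation sensitivity analysis is planned for the primary outcome only.

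**The concern.** A baby sent home on gastric tube feeds was still without the event when observation ended. Dropping such babies selects the analysis set on the outcome, after randomisation. If an intervention speeds up sucking, fewer babies in that arm should go home on a tube, so the comparator arm loses more of its failures and the estimated benefit shrinks. If tube discharge differs by arm for another reason, the exclusion can create a difference where none exists. The Blinding section says that clinical staff cannot be blinded, so such a difference cannot be ruled out by design.

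The protocol treats a similar problem differently elsewhere. Under Two-year assessments, children too severely delayed to complete the developmental test are kept and given a score of −4 SD. Here the babies who do not reach the endpoint are removed, and no planned analysis would show the consequence.

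**Working it through.** **The plan's own figure.** The only sample-size calculation (Sample size section) concerns % fat mass and time to full enteral feeds; none is given for full sucking feeds. The stated hazard ratio is 10/7 = 1.43. With a two-sided alpha of 0.0167 (sidedness assumed) and 90% power, Schoenfeld's formula, 4(z₁₋α/₂ + z₁₋β)²/(ln HR)², needs 423 events. With 480 events the power is 93.6%, so the claim of at least 90% reproduces. I borrow 1.43 below as a benchmark for sucking feeds; this is an assumption.

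**Inputs.** True HR 1.43 (above 1 means faster sucking feeds); 1:1 allocation for each factor (Allocation sequence generation); 240 per arm (Sample size). The proportion of control babies discharged on a tube, p₀, is not in the document, so I take 2%, 5%, 10% and 15%. The protocol names no model for this outcome; a Cox model is assumed.

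**Scenario A: tube discharge at a constant hazard μ, the same in both arms.** Let sucking feeds have hazards λ₀ = 1 and λ₁ = 1.43. The babies left after exclusion have event times with hazard λ + μ, so

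HR after exclusion = (λ₁ + μ)/(λ₀ + μ), with μ = p₀/(1 − p₀).

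For p₀ = 5%: μ = 0.0526 and HR = 1.4826/1.0526 = 1.41.

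**Scenario B: tube discharge falls late, on slow feeders.** Babies not sucking fully by a fixed time go home on a tube, with that time set so that a fraction p₀ of controls is affected. The affected fraction of treated babies is then p₀ to the power 1.43; for example 0.05^1.43 = 1.4%. Hazard ratios come from a large simulation (Weibull, shape 2). Power is at two-sided 5% with 240 per arm and 4,000 runs.

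| Controls affected | A: HR, exclusion | B: treated affected | B: HR, exclusion | B: HR, censoring | B: power, exclusion | B: power, censoring |
|---|---|---|---|---|---|---|
| 2% | 1.42 | 0.4% | 1.37 | 1.43 | 93% | 97% |
| 5% | 1.41 | 1.4% | 1.32 | 1.42 | 84% | 98% |
| 10% | 1.39 | 3.7% | 1.27 | 1.43 | 68% | 97% |
| 15% | 1.37 | 6.7% | 1.22 | 1.43 | 54% | 96% |

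On the log scale at 5% of controls, scenario B loses 1 − ln(1.317)/ln(1.43) = 1 − 0.275/0.358 = 23% of the effect. Scenario A loses 1 − ln(1.408)/ln(1.43) = 1 − 0.342/0.358 = 4%.

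**Scenario C: no effect on sucking, but tube discharge differs by arm.** With constant hazards λ + μ = λ/(1 − p), so HR after exclusion = true HR × (1 − p₀)/(1 − p₁). With a true HR of 1, 5% against 10% gives 0.95/0.90 = 1.06, and 5% against 15% gives 0.95/0.85 = 1.12. The spurious benefit goes to the arm with more tube discharges.

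**Scenario D: neither sucking nor tube discharge is affected.** Exclusion leaves the HR at 1.00. The simulated rejection rate was 4.5% to 6.0%, near the nominal 5%.

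**The case against.** Four points on the other side carry weight.

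- **The rule has a sensible purpose.** Because any discharge home stops the clock, keeping tube-fed babies without further change would score them as successes on the day they leave. The exclusion prevents that. This stands, and it means that deleting the exclusion alone would be no remedy.
- **The outcome is secondary.** Both primary outcomes and the sample size are untouched. This stands and limits the gravity of the point, although the outcome is named in the taste/smell hypothesis.
- **The size is unknown.** The document does not say how many babies go home on a tube, when, or why. If the reason is mainly local practice, these babies need not be the slowest feeders, and stratification by centre would largely balance them. Scenario A is closer to that case, and its bias is small.
- **The rule is openly stated.** The protocol also says that missing outcomes will not be imputed, and it describes no collection of tube-removal dates after discharge. The authors may have regarded these babies as having no observable endpoint. But a baby followed without the event until discharge carries usable time-to-event information, so exclusion is not needed.

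A reader might infer that the rule could reverse the direction of a real benefit. The formula in scenario C shows what that takes: even with tube discharge of 15% in controls against 5% in treated babies, the true HR must be below 0.95/0.85 = 1.12. Reversal thus needs a null or small true effect together with an arm difference in tube discharge, and nothing in the document points to that combination. With a true HR of 1.43, every case in the table is attenuated and none is reversed.

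**Conclusion.** The rule is wrong as written and should be changed. It excludes babies after randomisation because of their outcome, and it does not fit the protocol's commitment to analyse all eligible infants as assigned. The bias arises only if an intervention affects sucking or tube discharge, and it then runs mainly towards no effect.

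Its size rests on assumed proportions. Over 2–15% of controls, a true HR of 1.43 becomes 1.37 to 1.22 if tube discharge is concentrated among slow feeders, and 1.42 to 1.37 if it is not. If few babies go home on a tube, the distortion is minor. A reader might take the lower end of the range as the expected effect, or think the trial's main conclusions are at risk; the document supports neither.

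**What to change.** In Monitoring of nutritional intake, replace the exclusion and amend the sentence before it:

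1. Keep every randomised baby in the analysis of time to full sucking feeds.
2. Count discharge home as the event only when the baby is no longer on gastric tube feeds.
3. Name a time-to-event model for this outcome, with babies discharged on tube feeds censored at discharge without the event.
4. Add a sensitivity analysis that keeps these babies event-free beyond the longest observed time.
5. Report the number discharged on tube feeds in each arm.

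The cost is a change to two sentences and one extra model. The discharge date is already needed for days in hospital, and feeding status at discharge is already needed to apply the present exclusion. The drawback is that censoring at discharge may be informative. The good recovery of 1.43 in scenario B comes from a model in which censoring is uninformative by construction, so it does not settle this; the sensitivity analysis in step 4 is there for that reason. The change concerns the analysis only and implies nothing about feeding or discharge practice.
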